### Statistical methods

2.9

#### Quantitative statistics

2.9.1

All quantitative data analyses will be performed using standard statistical software (R, version 4.2). To ensure methodological rigor, the primary efficacy analysis will be conducted in accordance with the intention-to-treat (ITT) principle, encompassing all randomized participants regardless of adherence to the intervention protocols or study completion. A per-protocol (PP) analysis, restricted to participants who complete a pre-defined minimum number of intervention sessions, will additionally be performed as a sensitivity check to assess the robustness of the findings.

##### Descriptive statistics and baseline comparability

2.9.1.1

Baseline demographic and clinical characteristics will be summarized across all four groups. Continuous variables will be presented as means with standard deviations (SD) or as medians with interquartile ranges (IQR), depending on the normality of the data distribution as assessed by the Shapiro-Wilk test. Categorical variables will be reported as frequencies and percentages. Baseline differences among the four parallel groups will be examined using one-way analysis of variance (ANOVA) for normally distributed continuous data, the Kruskal-Wallis test for non-parametric data, and the Chi-square or Fisher’s exact test for categorical data.

##### Analysis of primary and secondary outcomes

2.9.1.2

To evaluate the individual and synergistic effects of the interventions across the three assessment time points (baseline, Week 12, and Week 24), linear mixed-effects models (LMMs) will be employed. LMMs are particularly well-suited to this trial design, as they accommodate repeated measures, account for intra-subject correlation, and appropriately handle missing data under the missing-at-random (MAR) assumption without necessitating listwise deletion. The outcome measures—including global cognitive function (MoCA), memory, executive function, EEG/ERP parameters, and physical performance metrics—will be modelled as dependent variables. Fixed effects will comprise Group (Combined Intervention, rTMS Only, DMI Only, Control), Time (T0, T1, T2), and the Group × Time interaction term, with the latter serving as the primary indicator of intervention efficacy over the study period. Participant identification will be specified as a random intercept to account for between-subject variability.

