-t₁: Initial screening phase to determine clinical eligibility based on MoCA, Geriatric Depression Scale (GDS-15), and Berg Balance Scale (BBS) inclusion criteria. T0: Baseline assessment conducted immediately prior to randomization. T1: Primary endpoint assessment conducted immediately following the 12-week intervention. T2: Follow-up assessment conducted 12 weeks post-intervention to determine durability of effects. MoCA, Montreal Cognitive Assessment; GDS-15, 15-item Geriatric Depression Scale; WMS-IV, Wechsler Memory Scale Fourth Edition; BBS, Berg Balance Scale; 6MWT, 6-Minute Walk Test; SF-12, 12-item Short Form Health Survey; EEG/ERP, Electroencephalography/Event-Related Potential; rs-fMRI, Resting-state Functional Magnetic Resonance Imaging.

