#### Primary outcome

2.4.1

The primary outcome measure is the change in global cognitive function from baseline (T0) to post-intervention (T1), assessed using the Montreal Cognitive Assessment (MoCA). The MoCA is a highly sensitive, 30-point screening tool specifically designed to detect mild cognitive impairment (MCI), assessing multiple cognitive domains including executive function, visuospatial ability, memory, attention, and language (Nasreddine et al., 2005). To determine the clinical relevance of any observed changes, we will apply a Minimal Clinically Important Difference (MCID) threshold. Based on recent clinimetric evaluations in older adults with cognitive impairment, an increase of ≥ 2 points on the MoCA will be considered a clinically meaningful improvement (Lindvall et al., 2024).

While the MoCA is less susceptible to ceiling effects than the Mini-Mental State Examination (MMSE) in MCI populations, some participants with very mild impairment (e.g., baseline scores of 24–25) may still approach the maximum score of 30, potentially masking further cognitive gains (Trzepacz et al., 2015). To mitigate this, our statistical analysis plan will incorporate Tobit regression models, which are specifically designed to handle censored data and adjust for potential ceiling effects, ensuring accurate estimation of the intervention’s true cognitive impact (Proust-Lima et al., 2007).

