##### Factorial analysis for synergistic effects

2.9.1.3

To directly address the study’s aim of elucidating synergistic mechanisms and to capitalize on the robust factorial design, a 2 × 2 factorial analysis will be nested within the models. The main effect of the rTMS factor (active vs. sham), the main effect of the DMI factor (active vs. sham), and the rTMS × DMI interaction effect on the primary outcome will be tested. A statistically significant positive interaction term will quantitatively support the hypothesis that the combined intervention produces benefits exceeding the additive effects of the individual modalities.

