### Outcome hierarchy and multiplicity adjustment

2.10

To address concerns about multiplicity, the trial outcomes are organized in a pre-specified hierarchy. The primary outcome is the change from baseline (T0) to post-intervention (T1) in MoCA total score. Three pre-specified key secondary outcomes, all analyzed as T0 to T1 changes paralleling the primary, are: (1) change in executive function, operationalized as the TMT-B/A ratio to control for motor speed, with TMT-B and TMT-A reported separately as supporting analyses; (2) change in P300, assessed by peak latency (ms) and peak amplitude (μV) at midline electrodes (Fz, Cz, Pz); and (3) change in BBS score. To control the family-wise Type I error rate across these three key secondary outcomes, the Holm-Bonferroni step-down procedure will be applied; effect estimates with 95% confidence intervals (unadjusted and adjusted) will be reported, with the adjusted p-values used for inference. T0 to T2 changes (durability) for all three key secondary outcomes, as well as all other pre-specified outcomes—including WMS-IV (memory), 6MWT (functional exercise capacity), SF-12 (quality of life), and rs-fMRI (DMN and frontoparietal connectivity)—are treated as supportive/exploratory and are interpreted with caution.

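### The designated primary efficacy term covers Week 12 and Week 24 together, although the primary endpoint is the Week 12 MoCA change alone

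*Protocol article*

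**What the plan says.** The endpoint is tied to Week 12 in three places. Section 2.4.1 defines it as the MoCA change from T0 to T1. Section 2.10 repeats this: "The primary outcome is the change from baseline (T0) to post-intervention (T1) in MoCA total score". The note to Table 1 labels the visits the same way: "T1: Primary endpoint assessment conducted immediately following the 12-week intervention". It describes T2 as a follow-up for durability.

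The analysis is described in section 2.9.1.2. To evaluate the interventions "across the three assessment time points (baseline, Week 12, and Week 24), linear mixed-effects models (LMMs) will be employed". The fixed effects are Group (four arms), "Time (T0, T1, T2), and the Group × Time interaction term, with the latter serving as the primary indicator of intervention efficacy", and the sentence ends by referring to the whole study period. The covariance structure is also given: "Participant identification will be specified as a random intercept to account for between-subject variability".

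Section 2.9.1.3 adds that "a 2 × 2 factorial analysis will be nested within the models", with both main effects and their interaction tested on the primary outcome. It names no visit for these contrasts and does not call them primary.

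On Week 24, section 2.10 classes as supportive or exploratory the "T0 to T2 changes (durability) for all three key secondary outcomes" and all other pre-specified outcomes. It does not expressly place the MoCA T0 to T2 change anywhere in the hierarchy.

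**The concern.** The endpoint and the test named as the main sign of efficacy do not cover the same visits. The null hypothesis of the full Group × Time term is that the arms do not differ in change at Week 12 and do not differ in change at Week 24. Rejecting it does not say which visit is responsible. Arms that are alike at T1 and differ only at T2 could therefore produce a positive result on the designated term while the stated endpoint shows nothing.

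The two can also disagree the other way, when a Week 12 effect partly fades. In either case the text supports two different p-values as the primary one: section 2.9.1.2 points to the overall term, and sections 2.4.1 and 2.10 point to the T0 to T1 change. That choice should not be open once data are in.

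**Working it through.** **1. Degrees of freedom.** Four groups and three visits give (4-1)(3-1) = 6 for Group × Time with Time as a factor. The T0 to T1 comparison of four groups needs 3. The other 3 belong to Week 24. If Time were instead a linear trend, the term would be a 3-df slope test, which does not isolate T1 either.

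**2. The plan's own figures (section 2.7).** 128/(1-0.20) = 160 reproduces the recruitment target. N = 128 is the result for a 1-df effect in a four-group factorial ANOVA with f = 0.25 (power 0.801). The repeated-measures interaction that the section names would need 40 (three measurements) or 48 (two), assuming a correlation of 0.5. The article gives neither the number of measurements nor the correlation, so the sample size does not settle which test is primary.

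**3. Assumptions for the illustration.** The article gives no MoCA SD or between-visit correlation. I take 32 per arm (the plan's number after dropout), a change-score SD of 1 at both visits, and a dance effect of 0.5 SD, so arm means of 0.5, 0, 0.5, 0. Then Σ(mean - grand mean)² = 4 × 0.25² = 0.25, and f = √(0.25/4) = 0.25, the plan's effect size read on the change score. The correlation between the T0-T1 and T0-T2 changes is 0.5, which is what a random intercept implies, or 0.7 as an alternative.

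**4. Test of T0 to T1.** Noncentrality = 32 × 0.25 = 8.0. With 3 and 124 df, power is 0.639, or 64%. With no effect at T1 it is 5%.

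**5. The 6-df term.** With effect multiples a at T1 and b at T2 and correlation r, noncentrality = 8 × (a² - 2rab + b²)/(1 - r²). At r = 0.5 this goes into a noncentral F with 6 and 124 × 2 = 248 df. At r = 0.7 the random-intercept F test no longer matches the data, so its rejection rate was simulated.

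| True pattern | Noncentrality, r = 0.5 | 6-df term, r = 0.5 | 6-df term, r = 0.7 | T0-T1 test |
|---|---|---|---|---|
| None at T1, full at T2 | 8 × 1/0.75 = 10.67 | 66% | about 76% | 5% |
| Full at T1, half at T2 | 8 × 0.75/0.75 = 8.0 | 52% | about 58% | 64% |
| Full at both | 8 × 1/0.75 = 10.67 | 66% | about 71% | 64% |
| Full at T1, none at T2 | 8 × 1/0.75 = 10.67 | 66% | about 76% | 64% |

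**6. A different effect pattern.** With the effect in the combined arm only (0.5 SD, between-visit correlation 0.5, 20,000 simulated trials) and present only at T2, the 6-df term was significant in 51.8% of trials and the T0-T1 contrast in 4.8%. In 47.4% of trials the 6-df term was positive and the T0-T1 contrast negative. Under the complete null both rejected in 5.0%.

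**The case against.** The article never prints the words joint, omnibus or 6 df. Section 2.9.1.2 is a general paragraph for all outcomes, and it includes the EEG measures, which have no T2 visit, so it may be meant as a description of the model family. Section 2.10 says that the key secondary outcomes are analysed as T0 to T1 changes in parallel with the primary, which suggests that a Week 12 analysis was intended. Which contrast is extracted from a stated model is often left to the analysis plan, which is not shown.

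Most of this is fair as evidence of intent, but it does not remove the conflict. The article does not leave the primary indicator unsaid: it names the interaction term, lists all three visits and refers to the whole study period. No passage names the T1 contrast as the primary test.

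The T2-only scenario is also extreme, since the protocol expects durability rather than delayed onset. It shows what the term can respond to, not what is likely.

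A reader might draw four stronger conclusions that the document does not support:
- That the term fails to test the endpoint at all. It contains the T1 contrast; it just does not isolate it.
- That the false-positive rate is inflated. Under the complete null it stays at about 5%.
- That power is lost generally, or for the endpoint on which the trial was sized. The loss appears when the effect partly fades, and section 2.7 sizes the trial on a repeated-measures interaction, not on a T0 to T1 contrast.
- That section 2.10 already declares the MoCA T0 to T2 change exploratory. It does not name it.

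**Conclusion.** The point holds as a mismatch between the primary endpoint and the designated primary term, and it should be corrected before analysis because it decides which p-value makes the trial positive. The mismatch follows from the text and from counting degrees of freedom, with Time taken as a factor.

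The percentages rest on assumed values: 32 per arm, 0.5 SD, and a correlation of 0.5 to 0.7. On those, a Week 24-only effect makes the term significant about 66% to 76% of the time against 5% for a Week 12 test. A half-fading effect costs power, about 52% to 58% against 64%. If the effect is fully sustained or gone by T2, the overall term has slightly more power, about 66% to 76% against 64%, but it draws part of that from T2.

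**What to change.** In section 2.9.1.2, write:

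> The primary test for MoCA is the single joint 3-df test of the Group × T1 (T0 to T1) coefficients from the three-visit model, not the overall Group × Time term. The factorial contrasts in section 2.9.1.3 are also evaluated at T1. The T2 contrasts, including MoCA T0 to T2, are supportive.

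The wording must define one test; a plural reference to T1 contrasts would leave open whether they are joint or separate. The last sentence also gives MoCA at T2 the place in the hierarchy that section 2.10 omits.

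The cost is a few lines of wording. The three-visit model, the data and the missing-data handling stay as they are. The downside is a small loss of power when an effect is fully sustained or has gone by T2.

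One point to check when the test is coded: a contrast taken from the model inherits the random-intercept covariance. At a correlation of 0.7 the T1-T2 change has variance 1 + 1 - 2 × 0.7 = 0.6. The model then pools to (1 + 1 + 0.6)/3 = 0.87 for a T0-T1 change whose variance is 1, which would make the contrast somewhat liberal. The 64% and 5% for the T0-T1 test above use the change score's own variance.

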#### Dance movement intervention

2.3.2

Participants in the Combined Intervention and DMI Only groups will participate in a structured Chinese Square Dancing program. Sessions will be held 3 times per week for 12 weeks, with each session lasting 60 minutes. The intervention emphasizes rhythm, coordination, memory of sequences, and social interaction. Participants in this group will receive in total thirty-six hours of intervention. A maximum of 10 participants will be enrolled in each DMI class to ensure performance quality. Instructors will use oral explanations and encouragements during the interventions.

Chinese square dancing movement programs have been applied within various populations showing evidence of benefits (Bisbe et al., 2020; Blumen et al., 2022; Zhu et al., 2018, 2022). Any 4 × 4 beats music can be used for dance intervention routine; participants will also be allowed to recommend music. The DMI will combine choreography and improvisation, single and partner strategies, including gentle body movements (consisting of limbs and spine movements) with special emphasis on rhythm and contralateral movement on both sides of the body to enhance coordination and stimulation between right and left cerebral hemispheres (Ho et al., 2015, 2020). The DMI routine contains repetition and improvisation; therefore, it will require memory, concentration and dual-task function to complete the dance correctly.

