#### Social activity control

2.3.3

To control for the social interaction and general engagement inherent in the DMI, participants in the rTMS Only and Control groups will attend time-matched sessions (60 minutes, 3 times per week) involving non-aerobic activities such as watching educational videos, listening to music, and engaging in supervised, non-strenuous group discussions.

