### Sample size

2.7

A priori power analysis (G*Power 3.1) was conducted for a four-group repeated measures ANOVA (interaction effect). To detect a medium effect size (f = 0.25) with a power of 0.8 and an alpha level of 0.05, a total sample of approximately 128 participants (32 per group) is required. To account for potential participant dropouts, we have factored in an anticipated attrition rate of 20% over the 24-week study period (12-week intervention plus 12-week follow-up). This 20% estimate is intentionally conservative and rigorously justified by previous longitudinal literature involving older adults with cognitive impairment. Systematic reviews of intensive, multi-modal non-pharmacological interventions (including aerobic exercise and neuromodulation protocols) in geriatric populations consistently report attrition rates ranging from 15% to 21%, typically due to transportation barriers, intervention fatigue, or unrelated emergent health issues (Di Lorito et al., 2020). Therefore, to ensure the trial remains adequately powered throughout the follow-up phase, we aim to recruit a final total of 160 participants (40 per group).

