##### Handling of missing data

2.9.1.5

Although LMMs intrinsically accommodate missing data, multiple imputation (MI) via chained equations will be applied as a supplementary sensitivity analysis if the overall missing data rate exceeds 10% (in light of the anticipated 20% attrition rate), thereby corroborating the validity of the primary ITT findings. For all analyses, a two-sided p-value of less than 0.05 will be considered statistically significant.

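### The stated model has no term for dance classes or social groups, so with any positive class ICC the DMI main effect gets too small a standard error and less than the stated 80% power

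*Protocol article*

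**What the plan says.** On delivery, Section 2.3.2 of the protocol article sets the class size: "A maximum of 10 participants will be enrolled in each DMI class to ensure performance quality". Sessions run three times a week for 12 weeks. Classmates share instructors, partner work and a facilitated sharing discussion. Routines are adapted to participants' abilities, and participants may suggest music. Section 2.3.3 describes the social control as time-matched sessions with videos, music and "engaging in supervised, non-strenuous group discussions", and gives no group size.

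On analysis, Section 2.9.1.2 specifies fixed effects for Group, Time and Group × Time, and for the random part: "Participant identification will be specified as a random intercept to account for between-subject variability". Section 2.9.1.3 tests the rTMS main effect, the DMI main effect and their interaction on the primary outcome. Section 2.9.1.4 lists age, gender, education and baseline MoCA as covariates. No class term, cluster-robust standard error, ICC or design effect appears.

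On size, Section 2.7 concludes that "a total sample of approximately 128 participants (32 per group) is required", and raises this to 160 for dropout.

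**The concern.** People who spend 36 sessions in the same class, with the same instructors and partners, may change together. Individual randomization does not prevent this, because the correlation arises after randomization through shared delivery. A participant intercept handles repeated measures within one person. It does not handle correlation between classmates.

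The DMI main effect compares people in dance classes with people in social sessions, so it lies wholly between classes. If class outcomes are positively correlated, the stated model gives this contrast too small a standard error, its test rejects too often under the null, and the true power is below the planned figure. A positive dance result would be open to that criticism. The same applies to dance-versus-social contrasts on the secondary outcomes, including the Berg Balance Scale, a key secondary outcome in Section 2.10.

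**Working it through.** **Inputs.** From Section 2.7: "To detect a medium effect size (f = 0.25) with a power of 0.8 and an alpha level of 0.05"; 128 completers; "anticipated attrition rate of 20% over the 24-week study period"; 160 recruited. From Section 2.9.1.5: "a two-sided p-value of less than 0.05 will be considered statistically significant". From Section 2.3.2: class size m of at most 10, so 80 dance participants need at least 80/10 = 8 classes. With 20% dropout, about 10 × 0.8 = 8 per class remain. The ICC is not in the article. I assume 0.01, 0.02, 0.05 and 0.10.

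**The plan's own figure.** A four-cell ANOVA with one numerator degree of freedom and noncentrality f² × N = 0.0625 × 128 = 8 (denominator df 124) has power 0.801, and 128 is the smallest N that reaches 0.80. Then 128/0.8 = 160. The stated numbers therefore reproduce as a single 2 × 2 factorial contrast among independent people, which means a design effect of 1. The article's label, a repeated measures interaction, does not give 128: with 4 groups, 3 times and an assumed correlation of 0.5 it gives about 40.

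**Design effect.** For a clustered side, DE = 1 + (m − 1) × ICC. The DMI contrast compares two halves of equal size, so its variance inflation is the average of the two sides: (1 + DE)/2 if only dance is clustered, DE if both are.

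**Type I error of the unadjusted test, m = 10:** 2 × [1 − Φ(1.96/√inflation)].

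| ICC | Inflation, dance only | Type I | Inflation, both | Type I |
|---|---|---|---|---|
| 0.01 | 1.045 | 5.5% | 1.09 | 6.0% |
| 0.02 | 1.09 | 6.0% | 1.18 | 7.1% |
| 0.05 | 1.225 | 7.7% | 1.45 | 10.4% |
| 0.10 | 1.45 | 10.4% | 1.90 | 15.5% |

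With m = 8 the type I error is 5.4% / 5.8% / 7.1% / 9.2% (dance only) and 5.8% / 6.6% / 9.2% / 13.3% (both).

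**Power at 128 completers, m = 8,** for a test with the correct standard error: noncentrality 8/inflation, df 1 and 124.

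| ICC | Inflation, dance only | Power | Inflation, both | Power |
|---|---|---|---|---|
| 0.01 | 1.035 | 79% | 1.07 | 77% |
| 0.02 | 1.07 | 77% | 1.14 | 75% |
| 0.05 | 1.175 | 74% | 1.35 | 68% |
| 0.10 | 1.35 | 68% | 1.70 | 58% |

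These figures ignore the loss from few class-level degrees of freedom. With both sides clustered there are 128/8 = 16 classes or groups in four cells, so about 16 − 4 = 12 df, and power is 71% / 68% / 61% / 51%.

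**Which contrasts are affected.** If Combined and DMI Only participants dance together, and the two social arms also meet together, the active-versus-sham difference is taken within a class and the class effect cancels. The rTMS effect and the interaction then keep their precision. If classes are arm-specific, every cell mean carries class variance and both are inflated like the DMI effect. The article does not say which applies.

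**Where the class term must act.** Classes form after baseline, so a class effect is present at T1 and T2 but not at T0. The primary outcome is the T0 to T1 change, and efficacy is judged on Group × Time. A class intercept that is constant over time subtracts out of T1 − T0 and leaves the standard error of that contrast essentially unchanged.

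**The case against.** Four objections have force.

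- **Size is unknown.** No ICC for MoCA change is given. At 0.01 with only dance clustered, type I error is about 5.5% and power about 79%, which is trivial. This stands: the omission is certain, its effect is not.
- **The social side is uncertain.** A reader might infer that the cap of 10 applies to both activities. It is stated for dance classes only. The social control also includes videos and music, and Section 2.2 contemplates make-up lessons, so stable membership is an inference. The figures with both sides clustered are therefore the upper scenario.
- **The labelled test may be unaffected.** A reader might infer that the stated power is wrong for the test it names, or that the interaction test is invalid. Section 2.7 says: "A priori power analysis (G*Power 3.1) was conducted for a four-group repeated measures ANOVA (interaction effect"). If arms share classes, the rTMS × DMI interaction is not inflated. The article does not support the stronger reading.
- **An analysis plan may add a class term.** Section 2.4.1 refers to one that is not shown, and Section 2.9.1.2 does not call the participant intercept the only random term. But the article itself sets out the fixed effects, a random effect, the covariates and a numerical sample size, and these do not match its own delivery format. This is a stated model that does not fit, rather than detail left out.

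**Conclusion.** The point holds for the DMI main effect and for dance-versus-social contrasts, on condition that the class ICC is positive. The direction is then certain: the standard error is too small and power is below 80%. The size rests on the assumed ICC and on whether social groups are stable and of similar size. Over ICCs of 0.01 to 0.10, type I error runs from about 5.5% to 16% and power from about 79% to 58%, before any loss of degrees of freedom. It is minor at the low end and material from about 0.05 upward. The documents do not establish that the rTMS effect or the interaction is affected. The plan should be corrected, but the design is not undermined.

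**What to change.** 1. Record dance-class and social-group ID prospectively for every participant.
2. Model clustering where it acts: either a class-by-time random effect on post-baseline visits, or a class random effect in a baseline-adjusted model of T1 MoCA. Make it partially nested if the social control is not run in stable groups. Use Kenward-Roger or Satterthwaite degrees of freedom.
3. State the social-group size, and whether Combined and DMI Only participants share classes (and likewise the two social arms). Sharing protects the rTMS effect and the interaction. It also lets active and sham participants compare stimulation sensations, which bears on the blinding assessment in Section 2.6.2, so the choice should be made openly.
4. Restate the power in Section 2.7 for the DMI main effect over an assumed ICC range.

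The cost is one or two ID variables, one model term and some text, with wider DMI intervals and a less favourable power statement. Enlarging the trial is not proposed. With both sides clustered at 10, restoring 80% power would take 128 × DE = 140 / 152 / 186 / 244 completers, or 175 / 190 / 233 / 305 recruited after dividing by 0.8, even before the loss of degrees of freedom.

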### Participants

2.2

Participants will be recruited from the Department of Rehabilitation at Handan Central Hospital. A convenience sampling method will be employed, with local physicians providing a list of potentially eligible patients diagnosed with MCI. All participants will provide written informed consent before enrollment. A family member or legal guardian will also be asked to co-sign the consent form. Participant data will be anonymized to ensure confidentiality. The data will be secured during the study and destroyed five years after the study completion.

Inclusion criteria: (1) Diagnosis of amnestic or multi-domain MCI by a specialist physician according to the National Institute on Aging-Alzheimer’s Association (NIA-AA) criteria. (2) Age between 50 and 85 years. (3) Montreal Cognitive Assessment (MoCA) score between 18 and 25. (4) Geriatric Depression Scale (GDS-15) score < 5. (5) Physically able to participate in dance activities without assistive devices and deemed at low risk for falls (Berg Balance Scale score ≥ 41). (6) Stable doses of any prescribed medications for at least 30 days prior to screening. (7) Sufficient visual and auditory acuity (with correction if necessary) to complete assessments and interventions. (8) Voluntarily agrees to participate and provides informed consent.

Exclusion criteria: (1) Diagnosis of dementia (any type). (2) Presence of major psychiatric conditions (e.g., major depressive disorder, schizophrenia) or neurological disorders (e.g., Parkinson’s disease, stroke) that could confound cognitive assessment. (3) Contraindications to rTMS (e.g., history of seizures, metallic implants in the head). (4) Regular participation in structured exercise (≥ 3 times per week) or another cognitive intervention program within the past six months. (5) Abuse of drugs or alcohol that could cause cognitive impairment.

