### The relationship between education level and intervention efficacy

3.5

Cognitive reserve, shaped by education, may modulate how older adults engage with combined cognitive-physical interventions. Because Chinese square dancing demands continuous attention, working memory, and spatial planning to synchronize complex movements with music, individuals with higher educational attainment may adapt more readily. We hypothesize that rTMS-induced modulation of cortical excitability may lower the cognitive threshold for learning these routines, potentially allowing adults with lower educational backgrounds to derive comparable benefits; this hypothesis will be tested in a pre-specified subgroup analysis.

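### The random-intercept model bases the T0–T1 MoCA standard error on an average over all three visit pairs, so the primary contrast is modestly miscalibrated if visit correlations differ

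*Protocol article*

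**What the plan says.** Section 2.9.1.2 of the protocol article chooses linear mixed models partly because "they accommodate repeated measures, account for intra-subject correlation". The fixed effects are Group, "Time (T0, T1, T2), and the Group × Time interaction term, with the latter serving as the primary indicator of intervention efficacy over the study period". On covariance it says only: "Participant identification will be specified as a random intercept to account for between-subject variability". It mentions no random slope, visit-specific variance, residual correlation or robust standard error.

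Section 2.10 ties the primary outcome to one pair of visits: "The primary outcome is the change from baseline (T0) to post-intervention (T1) in MoCA total score". Section 2.4.1 agrees. Section 2.9.1.3 nests the rTMS × DMI factorial tests in the same models. The significance rule in section 2.9.1.5 is: "For all analyses, a two-sided p-value of less than 0.05 will be considered statistically significant".

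**The concern.** The primary contrast concerns two visits, but the model also contains a third and makes all three share one variance and one correlation. The third visit therefore helps to set the standard error of a contrast it does not belong to. If T1 and T2 resemble each other more than T0 and T1 do, the T0–T1 interval is too narrow and the test rejects too often. If correlation fades with time, the interval is too wide and power is lost. This can happen even with complete data.

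The primary MoCA contrast and the synergy test are exposed, as are the TMT-B/A ratio and BBS, which also have three visits. The plan also relies on the mixed model to handle missing data under MAR, with 20% attrition expected. Likelihood-based validity under MAR needs a suitable covariance model.

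**Working it through.** **Inputs from the article.** Three visits, four equal arms, a participant random intercept, T0–T1 as the primary contrast, two-sided 5%. The sample size section reads: "To detect a medium effect size (f = 0.25) with a power of 0.8 and an alpha level of 0.05, a total sample of approximately 128". That total reproduces as a 1-df test in a four-cell factorial ANOVA with f = 0.25 (power 0.801), and 128 / (1 − 0.20) = 160. It only sets the scale here, at 32 to 40 per arm; the point does not depend on it.

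**Assumed inputs.** The article gives no MoCA SD and no between-visit correlation. The correlations below are assumptions, written r01/r02/r12 for T0–T1, T0–T2 and T1–T2, with SD 1 at each visit.

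**Formula.** Let Vjk be the variance of the difference between visits j and k, so Vjk = 2(1 − rjk) when the SDs are 1. With complete data, a person's within-person sum of squares equals one third of the sum of the three squared differences, on 2 df. Hence the residual variance estimates (V01 + V02 + V12)/6. The model's variance for any visit difference is twice that, the mean of the three V. So:

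- k = model SE / true SE for T0–T1 = √[(V01 + V02 + V12) / (3·V01)]
- true two-sided alpha = 2[1 − Φ(1.96·k)]

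**Results.**

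| r01/r02/r12 | V01, V02, V12 | mean V | k | alpha |
|---|---|---|---|---|
| 0.6/0.6/0.6 | 0.8, 0.8, 0.8 | 0.800 | 1.000 | 5.0% |
| 0.5/0.5/0.7 | 1.0, 1.0, 0.6 | 0.867 | 0.931 | 6.8% |
| 0.6/0.6/0.8 | 0.8, 0.8, 0.4 | 0.667 | 0.913 | 7.4% |
| 0.7/0.5/0.7 | 0.6, 1.0, 0.6 | 0.733 | 1.106 | 3.0% |

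**Simulation, single contrasts** (20,000 null trials, 32 per arm). Combined v Control, T0–T1, with the random intercept and then with a T0–T1-specific variance:

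- compound symmetry: 5.4% and 5.3%
- 0.5/0.5/0.7: 6.8% and 5.1%
- 0.6/0.6/0.8: 7.0% and 4.7%
- 0.7/0.5/0.7: 3.1% and 5.1%

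The 2×2 interaction on the T0–T1 change gave 6.9%, 7.2% and 2.8% in the last three patterns.

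**Simulation, omnibus Group × Time** (20,000 null trials, 40 per arm, complete data): 5.2% under compound symmetry, then 5.3%, 5.8% and 5.9%. A further run at 36 per arm gave 5.5% to 6.3% in patterns without compound symmetry. Averaging over visit pairs distorts a single contrast but largely cancels in the joint test.

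**Baseline covariate.** Section 2.9.1.4 adds baseline MoCA. With complete data it does not enter the within-person contrast. For 0.6/0.6/0.8 at 40 per arm (2,000 trials), rejection with the covariate was 7.2% for Combined v Control and 6.2% for the interaction. With dropout added (10% missing at T1, 20% at T2) it was 8.9% and 7.0%. At 2,000 trials each rate has a Monte Carlo error of about half a percentage point.

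**P300.** Table 1 schedules it at T0 and T1 only. There is one visit pair, so nothing is averaged.

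**The case against.** **The entry band.** A reader might infer that "Montreal Cognitive Assessment (MoCA) score between 18 and 25" narrows the spread at T0 but not later, and so makes unequal variances likely by design. The article does not support this. Table 1 and its legend place the inclusion MoCA at a separate screening visit, with another MoCA at T0. If a random-intercept model holds in the population, selection on the screening score restricts the person effect equally at T0, T1 and T2, and compound symmetry survives. Simulation with an assumed mean of 22, SD 2.5 to 4 and correlation 0.5 to 0.8 gave an SE ratio of 1.00 and alpha 5.0%. If the screening score were reused as T0, the ratio was 1.01 to 1.04 and the test slightly conservative.

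**Shared response.** A reader might also infer that varying treatment response makes T1 and T2 more alike and so inflates type I error, citing section 3.5: "Cognitive reserve, shaped by education, may modulate how older adults engage with combined cognitive-physical interventions". If treatment affects nobody, varying response cannot raise the T1–T2 correlation. Inflation then needs person-specific change unrelated to treatment. Section 3.5 motivates a subgroup analysis and says nothing about correlations between visits.

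**Which test is primary.** Section 2.9.1.2 calls the Group × Time interaction the main indicator of efficacy, and that omnibus test is only mildly affected. This objection stands for that test. It does not remove the problem for the T0–T1 contrast, which sections 2.4.1 and 2.10 make primary, or for the factorial interaction.

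**Detail left elsewhere.** A random intercept can be combined with structured residuals, and an analysis plan not shown may specify them. That is possible, so the text does not strictly force compound symmetry. But the article states one structure affirmatively and signals no other.

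**Conclusion.** The point holds as a conditional and modest one. As written, and with ordinary residuals, the model uses a pooled variance for the T0–T1 MoCA contrast and for the 2×2 interaction on that change. If the visit correlations are equal, nothing is lost. If they are not, type I error moves to about 7% when T1 and T2 are more alike, or about 3% when correlation decays with lag, under the assumed values above. The corresponding 95% intervals would cover about 93% or 97%.

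The article has no SDs or correlations, so neither direction nor size can be fixed from it. The stronger claim, that the design itself makes the primary test liberal, is not supported. Confidence is medium, and the change is worth making because it is cheap and removes a dependence on an untested equality.

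**What to change.** Replace the participant random intercept with an unstructured 3×3 within-person covariance over T0, T1 and T2, common to the arms. Use small-sample degrees of freedom, and name a fallback structure in advance in case the fit does not converge. Any term for dance class or session group stays separate.

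One consequence needs care. If the baseline MoCA covariate in section 2.9.1.4 is the T0 score, it should not stay in a MoCA model that also has T0 as a response with its own variance. A slope of one on it would fit T0 exactly and drive the T0 variance to zero. Either omit the covariate from that model, or keep it and model only T1 and T2 as responses, with an unstructured 2×2 covariance.

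The cost is small: six covariance parameters instead of two, estimable with 128 to 160 people, and one changed model statement. No data collection or recruitment changes. It should be fixed before outcome data are seen, because a covariance structure chosen afterwards is open to challenge.
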